**Fig. 1 Fig1:**
[figure not shown]
Standard Protocol Items: Recommendations for Interventional Trials (SPIRIT) figure displaying the pilot trial design and the outcome measurements. After screening for eligibility (t-1), women sign the informed consent form and complete the baseline questionnaire (t0). Participants are then randomized in the probiotic or placebo arm and receive either the probiotic food supplement or placebo. After randomization, filling in the baseline questionnaire and collecting maternal vaginal and stool samples, women start using either the probiotic food supplement or placebo. Measurements take place at 26–30 weeks of pregnancy (baseline(t0); 34–38 weeks of pregnancy (t1); 7 days after birth (t3), and 1 month after birth (t4)).

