#### Start of the intervention

Prior to the first home visit, the participant fills in the baseline questionnaire (see Fig. 1). During the first home visit, the participants receive the probiotic/placebo product and kits from the CI who is blinded to the intervention. The participant collects the first stool and vaginal samples at home prior to the start of taking the probiotic/placebo product. These samples are kept in the participant’s freezer and handed over to the CI or research assistant at time point 1 (t1) or t4. After stool and vaginal fluid collection, the participant starts with the probiotic/placebo product intake once per day until time of delivery.

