### Measurements and outcomes

#### Primary outcome

The primary outcome will be assessed as follows: feasibility will be assessed in terms of (A) recruitment (quantitative and qualitative), (B) retention (quantitative) and acceptability will be assessed in terms of (C) compliance (quantitative) and (D) participants’ impressions and experiences during the pilot trial (quantitative).

The primary outcome of a full RCT would include effectiveness of the probiotic, compared to placebo, in reducing anxiety and depressive symptoms during pregnancy. For that reason, key outcome measures of this pilot study will inform whether or not to proceed with a full trial after this study, and if so, the revisions that should be made to the study protocol before conducting a full RCT. These outcomes include (B) retention rate, (C) compliance (i.e. proportion of participants taking ≥ 80% probiotic/placebo and proportion of participants filling in electronic questionnaires at all time points) and (D) participants’ experiences of participation and perspectives on joining this and future probiotic trials. Table 1 shows the outcomes, progression criteria (where applicable), key outcome measures and time points for each outcome of this pilot study.

**Table 1 Tab1:** Primary outcomes, (key) outcome measures, time points for each outcome and progression criteria for a full RCT

Primary quantitative outcomes	Outcome measure and time point for each outcome	Progression criteria for full RCT^a^
A) Recruitment	1) The proportion of contacted participants scoring above the threshold for anxiety or depressive symptoms and who accept the invitation to participate in the pilot trial throughout the study	30 participants recruited in 6 months
	2) The number of participants recruited at each site	No criteria set
B) Retention rate	2) The proportion of participants completing the study from enrolment (t0) to follow up (t4)*	≥ 90% of enrolled participants^b^
C) Compliance	3) The proportion of participants taking ≥ 80% probiotic/placebo product between t0 and t1*	90% of participants^c^
	4) The proportion of participants filling in electronic questionnaires at all time points (t0, t1 and t4)*	90% of participants
	5) The proportion of participants filling in the cry diary at t4	90% of participants
	6) The proportion of participants filling in evaluation form at t4	90% of participants

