Maternal lifestyle	Smoking (yes/no)	Baseline value	Proportion of participants smoking
	Alcohol (yes/no)	Baseline value	Proportion of participants drinking alcohol
Pregnancy characteristics	Occurrence of infections during pregnancy	Final value	Proportion of participants reporting infections (i.e. influenza, fever, diarrhea) throughout the study
Delivery characteristics	Gestational age	Final value	Gestational age at delivery
Pregnancy and delivery complications	Number of pregnancy and delivery complications (i.e. hypertensive disorders of pregnancy (pregnancy induced hypertension, preeclampsia, eclampsia, hemolysis - elevated liver enzymes - low platelet count (HELLP) syndrome), gestational diabetes mellitus, preterm birth, cesarean section, retention placentae, hemorrhage postpartum, small or large for gestational age (birth weight < p10 or > p90), puerperal fever, prolonged labor, premature rupture of membranes)	Final value	Proportion of participants diagnosed with pregnancy or delivery complications at delivery
Infant antibiotic use	Number of antibiotics used	Final value	Proportion of infants receiving antibiotics during first month of life
Depression	Edinburgh Postnatal Depression Scale (EPDS) score	Change from baseline to t1 and t4	Mean (SD)/median (IQR)
Depression/cognitive reactivity	Leiden Index of Depression Sensitivity-Revised (LEIDS-R) score	Change from baseline to t1 and t4	Mean (SD)/median (IQR)
Pregnancy related anxiety	Pregnancy Related Anxiety Questionnaire-Revised (PRAQ-R) score	Change from baseline to t1	Mean (SD)/median (IQR)
General anxiety	State-trait Anxiety Inventory (STAI-S) score	Change from baseline to t1 and t4	Mean (SD)/median (IQR)
Pregnancy-related daily hassles	Pregnancy-related daily hassles (PES) score	Change from baseline to t1 and t4	Mean (SD)/median (IQR)
General daily hassles/stress	Daily Hassles List (APL) score	Change from baseline to t1 and t4	Mean (SD)/median (IQR)
Mother to infant bonding	Maternal Antenatal Attachment Scale (MAAS) score	Change from baseline to t1	Mean (SD)/median (IQR)
	Maternal Postnatal Attachment Scale (MPAS)	Change from t3 to t4	Mean (SD)/median (IQR)
Biological samples	Maternal fecal samples (microbiota)	Change from baseline to t1	Relative abundance and diversity of bacteria at phylum up to genus level
	Maternal vaginal samples (microbiota)	Change from baseline to t1	Relative abundance and diversity of bacteria at phylum up to genus level

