	Maternal hair (cortisol)	Change from baseline to t1	Mean (SD)/median (IQR)
	Fecal sample infant (microbiota)	Change from t3 to t4	Relative abundance of bacteria at phylum up to genus level
Cry diary	Duration (hours/minutes) of crying during 3 days	Final value	Mean (SD)/median (IQR)

^a^Baseline: t0; time point 1: t1, time point 3: t3, time point 4: t4

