#### Maternal stress

##### Pregnancy-related daily hassles

Pregnancy-specific daily hassles/stress are assessed with the Dutch translation of the Pregnancy Experience Scale (PES), a 43-item self-report inventory that measures maternal appraisal of daily, pregnancy-specific hassles and uplifts (Cronbach’s alpha between 0.91 and 0.95 when applied in its original language) [53]. The Dutch translation has been commonly used among pregnant Dutch women [54, 55]. Women rate the degree to which specific experiences constitute a hassle and uplift on a 5-point scale. The total score is the sum of intensities of hassles divided by the sum of intensities of uplifts; higher values indicate greater negative emotional bearing towards pregnancy hassles.

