#### Infant intestinal microbiota

Parents will collect two infant fecal samples at home on weeks 1 and 4 using similar collection methods to those applied in our previous studies [36, 38], to measure the relative abundance of infant intestinal bacteria. Samples will be immediately stored by the participants at − 20 °C, collected by investigators at t3 and taken back to the University for storage at − 80 °C. The microbial composition of the stool samples will be analyzed using PCR sequencing methods.

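### Postnatal bonding (MPAS) and infant microbiota are analysed as t3-to-t4 change, both visits after intake has ended, so a lasting arm difference cancels and a fading one reverses sign

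*Protocol article*

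**What the plan says.** - **Exposure.** Under Start of the intervention, after the first samples "the participant starts with the probiotic/placebo product intake once per day until time of delivery".
- **Visits.** The Fig. 1 legend places the two postnatal visits at "7 days after birth (t3), and 1 month after birth (t4").
- **Metric.** In Table 2 (Secondary outcomes) the entry for MPAS is "Change from t3 to t4", and the row "Fecal sample infant (microbiota") has the same entry. No other metric is given for either outcome.
- **Baseline.** The Table 2 footnote reads "Baseline: t0; time point 1: t1, time point 3: t3, time point 4: t4". Neither MPAS nor infant stool can exist at t0.
- **Infant sampling.** The section Infant intestinal microbiota says "Parents will collect two infant fecal samples at home on weeks 1 and 4" and gives the purpose as measuring relative abundance, which is a level.
- **Questionnaire visits.** One compliance measure in Table 1 is "The proportion of participants filling in electronic questionnaires at all time points (t0, t1 and t4"), with no t3.
- **Model.** Statistical analysis, Secondary outcomes, names the t test, the Mann–Whitney test and an ANCOVA with the baseline score as covariate.

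**The concern.** The Objectives and Secondary outcomes sections ask whether maternal intake, compared with placebo, affects bonding and infant microbiota. The Discussion expects an influence on bonding already in the early postnatal period, and it argues about infant microbiota in terms of higher or lower abundance. These are questions about how the arms differ in level after exposure.

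Subtracting t3 removes whatever part of the effect is already present one week after birth, and that is when an effect of prenatal intake might first be seen. Table 2 treats comparable outcomes differently. Infant crying, also measurable only after birth, is analysed as a final value. The prenatal scales and the maternal stool and vaginal samples are analysed as change from the pre-intake t0.

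What is at stake is the usefulness of these outcomes. The Objectives say they are collected so that effects and mechanisms can be assessed properly in a later definitive trial. A metric that can show no difference, or a reversed one, when the arms do differ works against that.

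**Working it through.** The document states no figure that depends on this metric, so there is nothing to reproduce. The check is algebraic, with a simulation for scale.

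**Inputs from the document:** 20 women per arm (Sample size calculation); significance level 0.05 (Statistical analysis); visit times and end of intake as cited above.

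**Assumptions, not in the document:** two-sided testing; equal unit SD at both visits; arm difference D = 0.8 SD at t3; t3–t4 correlation ρ of 0.3, 0.5 or 0.7; a fraction k of the effect remaining at t4; normally distributed scores.

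**Change metric.** With D3 = D and D4 = kD, the expected arm difference in (t4 − t3) is kD − D = (k − 1)D.
- k = 1 (lasting): 0 × 0.8 = 0.00 SD
- k = 0.5 (half waned): −0.5 × 0.8 = −0.40 SD
- k = 0 (fully waned): −1 × 0.8 = −0.80 SD

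The contrast is positive only if k > 1. The variance of the change is 2(1 − ρ) times that of a single visit: 1.4, 1.0 and 0.6 at ρ = 0.3, 0.5 and 0.7.

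**ANCOVA with t3 as covariate.** With equal SDs the adjusted difference is about kD − ρD = (k − ρ)D. For k = 1 this is 0.7 × 0.8 = 0.56, 0.5 × 0.8 = 0.40 and 0.3 × 0.8 = 0.24 SD.

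**Simulation** (20 per arm; three entries are for ρ = 0.3, 0.5, 0.7):

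| k | Change: difference | Change: rejection rate | t4 value: difference | t4 value: rejection rate | ANCOVA on t3: difference |
|---|---|---|---|---|---|
| 1 | 0.00 | 0.05, 0.05, 0.05 | 0.80 | 0.70, 0.69, 0.69 | 0.57, 0.40, 0.24 |
| 0.5 | −0.40 | 0.18, 0.24, 0.36 | 0.40 | 0.23, 0.23, 0.23 | 0.16, −0.01, −0.17 |
| 0 | −0.80 | 0.55, 0.69, 0.89 | 0.00 | 0.05, 0.05, 0.05 | −0.24, −0.40, −0.56 |

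For k = 1 the power of the t3-adjusted ANCOVA is 0.40, 0.26 and 0.16. A normal approximation gives 0.72 for the t4 comparison, in line with the simulated 0.69–0.70. The last row shows why the t3 value is needed as well as the t4 value: an effect gone by one month is visible only at t3, where the expected difference is still 0.80 SD.

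**Is MPAS collected at t3?** Secondary outcomes says all questionnaires except the cry diary are electronic, so MPAS is electronic. Table 1 lists electronic questionnaires at t0, t1 and t4, while the MPAS row in Table 2 presupposes t3. The two entries do not agree.

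**The case against.** The strongest reply concerns weight. These are exploratory secondary outcomes of a 40-woman feasibility pilot. The protocol sets no success criteria for them, calls their analysis preliminary, and ties no progression criterion to them. The full trial would have anxiety and depressive symptoms as its primary outcome, and its sample size rests on depressive symptoms. The raw values at both visits would be kept and could be compared later. All of this stands, and it limits the severity. It does not make the stated metric answer the stated question.

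A second reply is that the infant microbiota entry may be a single table cell at odds with the text, since the section on infant samples and the aggregation column of Table 2 both speak of relative abundance, and that an analysis plan not shown may compare levels. That is possible. But the table states the metric explicitly and gives no other, so it needs correcting either way.

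A reader might also infer more than the document supports:
- **That two of the six secondary objectives are lost.** Bonding is also measured by the antenatal scale (MAAS) as change from t0 to t1, which is unaffected.
- **That power always equals alpha.** That requires D3 = D4. The document does not say the effect is constant from day 7 to one month, and a waned effect gives a non-zero contrast of the wrong sign.
- **That the MPAS metric cannot be computed.** The schedule is in Fig. 1, which is not available here, so collection at t3 cannot be settled.
- **That the pregnancy-specific hassles scale, scheduled to t4, is the same fault.** It has a pre-intake baseline, so nothing cancels. It is a separate question.

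**Conclusion.** The concern holds as a fault in the stated metric. For MPAS and infant microbiota, the t3-to-t4 change estimates D4 − D3 and not the effect of prenatal intake. This follows from the visit times and the end of intake, whatever the effect size. An ANCOVA that used t3 in place of a baseline would not repair it. It would shrink a lasting effect of 0.8 SD to between 0.24 and 0.57 SD over the correlations tried.

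The power figures depend on the assumed 0.8 SD, the correlations and normality. They illustrate scale and do not predict results for this trial. For bacterial abundances the cancellation applies on whatever scale the change is taken, but the power figures do not carry over directly.

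The scope is the infant microbiota objective and the postnatal half of the bonding objective. The primary feasibility and acceptability aim and the progression criteria are untouched, and the document does not show that design errors would carry into the definitive trial. Severity: should be fixed.

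**What to change.** 1. In Table 2, replace the metric for MPAS and infant fecal microbiota with the values at t3 and at t4, each compared between arms, without subtracting or adjusting for t3. Antenatal MAAS at t0 may serve as a covariate for MPAS.
2. Keep the t3-to-t4 change, if wanted, as a description of development only.
3. State whether MPAS is collected at t3, and reconcile Table 2, Fig. 1 and Table 1 on this. If it is not collected, analyse the t4 value alone.
4. Leave the Table 1 questionnaire criterion as it stands. It is a starred key progression criterion, 35 women had already consented and 18 had completed at submission, and the Amendments section requires ethics committee approval for changes to primary outcomes.

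The cost is a change of wording in Table 2 and the secondary analysis text. No new data or visits are needed. The change is best recorded before the randomization code is released, which the protocol defers until the last participant has finished.

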### Psychological parameter for screening

#### Suicidality risk

The Mini International Neuropsychiatric Interview (MINI) is used to determine a positive diagnosis according to the main *Diagnostic and Statistical Manual* (DSM)-III-R/IV Axis I disorders. The Dutch translation [39] of the clinician-rated version of the MINI will be used [40]. The Dutch translation has had good validity in previous studies [41, 42]. Suicide risk will be measured using six screening questions from this tool. High suicidal risk is defined as a positive response on questions C4 or C5 or (C3 + C6) [40].

### Psychological parameters for secondary objectives

#### Maternal depression

##### Edinburgh Postnatal Depression Scale

Symptoms of depression are measured pre and post intervention through the Edinburgh Postnatal Depression Scale (EPDS). The EPDS is a validated tool that screens for antenatal and postnatal depressive symptoms [43]. It consists of 10 items related to how the participant has felt over the past 7 days rated on a 4-point scale. The Dutch translation of the questionnaire has demonstrated excellent psychometric properties, including high test-retest reliability and concurrent validity among pregnant women in the Netherlands [44]. A sum score of 10 or more is believed to represent the presence of mild depressive symptoms as determined in a Dutch antenatal sample, yielding respectively 70% and 96% sensitivity and specificity [44].

##### Leiden Index of Depression Sensitivity-Revised

This measure is included because an earlier study using the Leiden Index of Depression Sensitivity-Revised (LEIDS-R) found that the intake of probiotics significantly reduced negative thoughts associated with sad mood [28]. The LEIDS-R is a validated tool that measures perceived cognitive reactivity to sadness, as a predictor of depression and will be applied in its original language (Dutch) [45–47]. The 34-item self-report includes six subscales: hopelessness/suicidality, acceptance/coping, aggression/hostility, control/perfectionism, risk aversion and rumination. Participants rate the extent to which each statement applies to them on a 5-point scale, ranging from “not at all” to “very strongly”. A higher total score indicates stronger cognitive reactivity.

#### Maternal anxiety

##### Pregnancy Related Anxiety Questionnaire-Revised

Pregnancy-specific anxiety is measured using the Pregnancy Related Anxiety Questionnaire-Revised (PRAQ-R). The PRAQ-R is a validated 10-item tool that screens for pregnancy-related anxiety in pregnant women and will be applied in its original language (Dutch) (Cronbach’s alpha between 0.79 and 0.88) [48]. Questions concern specific fears and worries related to pregnancy It is a shortened version of the 34-item questionnaire [49]. The PRAQ-R consists of three subscales: “fear of bearing a physically or mentally handicapped child” (“child-related anxiety”, 4 items), “fear of giving birth” (3 items) and “concern about one’s appearance” (3 items). Scales range from 1 (absolutely not relevant) to 5 (very relevant). The PRAQ-R has no established cutoff point; higher scores indicate higher levels of anxiety.

##### State-trait Anxiety Inventory

General anxiety is measured using the State-trait Anxiety Inventory (STAI-S). This self-report questionnaire evaluates prenatal anxiety in women [50] and the Dutch translation has good validity and reliability [51]. The STAI-S consists of 20 statements related to feelings of anxiety. Women indicate how they feel at the present moment on a 4-point scale. Scores are summed up and higher scores imply more general feelings of anxiety. A cutoff > 40 in STAI has 80.95% and 79.75% sensitivity and specificity in the third trimester of pregnancy to detect anxiety disorder [52].

#### Maternal stress

##### Pregnancy-related daily hassles

Pregnancy-specific daily hassles/stress are assessed with the Dutch translation of the Pregnancy Experience Scale (PES), a 43-item self-report inventory that measures maternal appraisal of daily, pregnancy-specific hassles and uplifts (Cronbach’s alpha between 0.91 and 0.95 when applied in its original language) [53]. The Dutch translation has been commonly used among pregnant Dutch women [54, 55]. Women rate the degree to which specific experiences constitute a hassle and uplift on a 5-point scale. The total score is the sum of intensities of hassles divided by the sum of intensities of uplifts; higher values indicate greater negative emotional bearing towards pregnancy hassles.

##### General daily hassles/stress

General daily hassles/stress are evaluated using the Dutch *Algemene Problemen Lijst* (Everyday Problem List) (APL). The APL measures the rate of occurrence and (negative) valence of daily hassles in the past 2 months (test–retest reliabilities between 0.76 and 0.87 among Dutch mothers) [56]. The APL consists of 49-items rated on a 4-point Likert scale. The total sum of the extent to which daily hassles bothered participants is divided by the frequency of daily hassles. Higher scores indicate more perceived stress due to daily hassles by the individual.

#### Mother-to-infant bonding

##### The Maternal Antenatal Attachment Scale

The Maternal Antenatal Attachment Scale (MAAS) assesses a mother’s bonding with her fetus. Previous studies have shown good psychometric properties of the Dutch translation in Dutch pregnant women [57]. The MAAS consists of 19 items divided into two subscales: “quality of attachment” (11 items) and “intensity of preoccupation” (8 items). Scales range from 1 (low bonding) to 5 (high bonding) [58]. Higher sum scores reflect higher-quality bonding and greater preoccupation with the unborn child.

##### The Maternal Postnatal Attachment Scale

The Maternal Postnatal Attachment Scale (MPAS) assesses the strength of the mother-to-infant bonding. The Dutch version of the MPAS has been demonstrated to be a valid and reliable tool for use in Dutch women during the postnatal period [59]. The MPAS questionnaire consists of 19 items, divided over three subscales: “quality of attachment”, “absence of hostility” and “pleasure in interaction” [60]. Women score the items on a 5-point Likert scale: 1 (low bonding) to 5 (high bonding). A higher sum score on the MPAS indicates higher quality mother-to-infant bonding.

### Behavioral parameter

#### Infant crying

##### Baby’s Day Diary

Barr’s standardized 24-h behavior diary to record infant crying, fussing and unsoothable crying will be used at 4 weeks of age for 3 days consecutively [61]. Barr’s behavior diary has been widely used and is validated against audio recordings with satisfactory results [61, 62]. The Dutch translation of the Baby’s Day Diary has been previously used in research [37, 38]. Mothers will fill in the Baby’s Day Diary at home on 3 days consecutively and will send a digital copy of the diary to the investigators. Excessive crying is determined as crying for ≥ 3 h per day on 3 constituent assessment days, to investigate the clinical implications of the results [63].

### Biological parameters

#### Maternal hair cortisol

A strand of around 50 hairs per person will be collected from the posterior vertex [64] at 4 weeks for postpartum cortisol analysis, in concordance with previously validated methods of collection and analysis of hair. The CI will cut the hair with scissors, as close as possible to the participant’s scalp. The hair closest to the scalp represents the most recent part of pregnancy. The sampling site is not visible afterwards, as the hair growing above covers it. After collection, 1 cm of the strand of hair that was closest to the scalp will be removed. The strand will then be divided into two segments for analysis, representing (1) the period during the last 8 weeks of probiotic or placebo intervention (2 cm) and (2) 2 months before the intervention (2 cm). Hair grows approximately 1 cm a month and therefore 2 cm will cover 8 weeks of probiotic or placebo intake. Hair cortisol will be analyzed using the procedure described by Manenschijn, Koper, Lamberts & van Rossum in 2011 [64]. A correction factor will be applied to account for the potential influence of differences in hair weight. Participants will record on a data form any intake of oral corticosteroids during pregnancy and other potential confounding factors. The hair and accompanying form will be securely stored together with the hair sample at the Sponsor’s site.

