## Methods

### Trial design

This probiotic intervention project in mothers and their infants is a double-blind, randomized pilot trial (RCT) (probiotic intervention versus placebo). Forty healthy pregnant women (≥ 18 years of age) with at least mild depressive symptoms and/or anxiety in the late second/third trimester of an uncomplicated pregnancy (≥ 26 and ≤ 30 weeks gestation) will be enrolled in this study (see Fig. 1). Participants will orally consume a probiotic multispecies mixture (Ecologic® Barrier; 2,5 × 10^9^ colony forming units (CFU)/g per dosage; daily dosage 2 g) once daily, or a placebo, for 8–14 weeks consecutively (depending on the time of delivery). Detailed information on the intervention components is provided under “Intervention procedures”. For more information on the protocol items, please refer to the Standard Protocol Items: Recommendations for Interventional Trials (SPIRIT) checklist (Additional file 1).

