### Inclusion and exclusion criteria

The total sample of 40 healthy pregnant women will be recruited in the region of Wageningen and Nijmegen, The Netherlands. In order to be eligible to participate in this pilot trial, women must meet all of the following inclusion criteria:At least mild symptoms of depression or anxiety.Start daily probiotic/placebo product intake between 26 and 30 weeks gestational age and continue until delivery. The lower limit of ≥ 26 weeks and the upper limit of 30 weeks allow time to complete at least 8 weeks of probiotic intake prior to delivery. Gestational age is based on last menstrual period and the early ultrasound scan.

A potential participant who meets any of the following exclusion criteria will be excluded from participation in this pilot trial:Multiple pregnancy (increased obstetric risk).High suicidal risk according to suicidality subscale score on the MINI (see screening).Illegal drug use.History of psychoses and bipolar disorder.Inflammatory bowel disease (i.e. ulcerative colitis, Crohn’s disease).Other autoimmune disorders and/or treatment with immunosuppressive therapy.Known pre-existing diabetes mellitus, hyperemesis gravidarum, hypertensive disorders or liver or renal disease.Malignancy and/or treatment with radiation or chemotherapy.History of major gastro-intestinal surgery (e.g. colectomy).Hypersensitivity or allergy to any ingredients in the probiotic/placebo product.History of using oral multi-species probiotic Ecologic® Barrier.Presently using food containing probiotics (e.g. Actimel) and not willing to stop these at least 2 weeks prior to the start of the probiotic/placebo product intake.No mastery of the Dutch language.

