#### Intake procedure

Participants in the probiotic and placebo intervention groups are provided with 108 sachets (one for each day of the intervention, total of 3,5 months). The contents of the sachets need to be dissolved in 100 mL water, milk or yoghurt. The solution containing the probiotic/placebo is to be ingested orally, preferably on an empty stomach. The participant will be advised to take the probiotic/placebo 2–3 h after antibiotic ingestion if taking antibiotics. The sachets are stored at room temperature in their original package.

The full RCT will not investigate probiotics as a single treatment, but will explore their properties as a food supplement in addition to patients’ current treatments, if applicable. Hence, the use of any kind of co-medication, therapy (e.g. cognitive behavior therapy) or alternative therapy (e.g. yoga, mindfulness, tai chi, etc.) is allowed and will be reported accordingly. Participants are requested to discontinue any other probiotic (such as probiotic yoghurts) two weeks prior to the start of the intake of the probiotic/placebo product and to refrain from taking any other probiotics during the whole trial period.

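### Read as adjacent pieces, the hair segment labelled pre-intervention overlaps intake by 0–75%, so the cortisol baseline is partly a post-randomisation value

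*Protocol article*

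**What the plan says.** The protocol article, under Maternal hair cortisol, takes hair "at 4 weeks for postpartum cortisol analysis", and then "1 cm of the strand of hair that was closest to the scalp will be removed". The remaining strand is divided into two pieces, representing "the last 8 weeks of probiotic or placebo intervention (2 cm) and (2) 2 months before the intervention (2 cm". The reason given for the length is that "Hair grows approximately 1 cm a month and therefore 2 cm will cover 8 weeks of probiotic or placebo intake". Nothing there moves the second piece according to when a woman began the product.

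Trial design says that intake runs "for 8–14 weeks consecutively (depending on the time of delivery". The inclusion criteria say "Start daily probiotic/placebo product intake between 26 and 30 weeks gestational age and continue until delivery". Intake procedure supplies "108 sachets (one for each day of the intervention, total of 3,5 months".

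In Table 2, the row "Maternal hair (cortisol" has as its metric the change between t0 and t1. The Fig. 1 legend puts t1 at 34–38 weeks of pregnancy, and Adherence assessment puts it after 8 weeks of intake. Table 1 lists hair collection at t4 only. The statistical section names two-group tests and also an ANCOVA with the baseline score as covariate.

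**The concern.** The two segment labels can both be true only if intake lasted about 8 weeks, which is the lower end of the stated range. For a woman with longer intake, the piece meant to show cortisol before the product contains hair grown while she was taking it.

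Because hair is collected only at t4, this piece is the only possible baseline. If the probiotic lowers cortisol, the baseline in the probiotic arm is lowered too. Subtracting it, or adjusting for it, then removes part of the effect being looked for. The amount removed depends on each woman's start and delivery dates, so no single correction factor repairs it. The article collects secondary outcomes so that mechanisms can be assessed properly in the definitive trial, and a misplaced baseline would be carried into that trial.

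**Working it through.** **Inputs, all from the article:** hair cut 4 weeks after birth; 1 cm discarded; two pieces of 2 cm; growth about 1 cm a month; start at 26–30 weeks of gestation; intake until delivery, 8–14 weeks.

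**The article's own figures reproduce.** 2 cm × 4 weeks/cm = 8 weeks. Duration: 40 − 26 = 14 weeks and 38 − 30 = 8 weeks.

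**Position of the pieces, counted back from delivery.** The discarded 1 cm is the 4 weeks after birth. Piece 1 (1–3 cm from the scalp) covers 0–8 weeks before delivery. Piece 2 (3–5 cm), if adjacent, covers 8–16 weeks before delivery.

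**Exposed share of piece 2.** With D weeks of intake, share s = max(0, min(D, 16) − 8)/8. With calendar months (about 4.35 weeks per cm), piece 2 begins 3 × 4.35 − 4 = 9.04 weeks before delivery and spans 8.70 weeks, so s = max(0, D − 9.04)/8.70 for these durations.

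| D (weeks) | s at 4 weeks/cm | s with calendar months |
|---|---|---|
| 8 | 0% | 0% |
| 10 | 25% | 11% |
| 12 | 50% | 34% |
| 13 | 62.5% | 45.5% |
| 14 | 75% | 57% |

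**Averages.** The article gives no distribution of durations, so two assumptions are shown:
- Durations spread evenly over 8–14 weeks: mean D = 11, so mean s = 3/8 = 37.5% (23.5% with calendar months).
- Starts spread evenly over 26–30 weeks with birth at 40: mean D = 12, so mean s = 4/8 = 50% (34% with calendar months).

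**Sensitivity to growth rate.** This is an assumed range, since the article gives only 1 cm. At 0.8 cm per calendar month, s is 0% at D = 12 and 16% at D = 14. At 1.2 cm it is 71% and 98%.

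**Effect on the contrast.** Suppose an effect that is constant from the first sachet. A change score keeps 1 − s of it: 100% at D = 8, 50% at D = 12, 25% at D = 14. An ANCOVA keeps 1 − b × s, where b is the slope on baseline. The article gives no b; at s = 50%, the share kept runs from 100% (b = 0) to 50% (b = 1), and is 75% at b = 0.5.

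**Table 2 label.** Take a start at 26 and delivery at 40 weeks. The period t0 to t1 is weeks 26–34. Piece 1 covers weeks 32–40 and holds 2 of those 8 weeks. Piece 2 covers weeks 24–32 and holds 6 of them. In this case the supposed baseline contains more of the t0–t1 period than the supposed outcome does.

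**The case against.** Five points can be made for the plan.

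- **Adjacency is inferred.** The article says that the strand is divided in two and names the period each piece represents; it does not state where the second cut falls. A detailed cutting instruction may exist in material not shown. This stands as a condition on the finding. Still, the only hair said to be removed is the 1 cm at the scalp, and the stated reasoning uses a fixed 8 weeks, so adjacency is the natural reading.
- **The overlap is not the larger part for most women.** A reader might infer that the piece mostly grew during intake. The figures do not support that: s passes one half only when intake exceeds 12 weeks (about 13.4 with calendar months). Nor is one start and delivery pair, such as 30 and 38 weeks, the only clean case. Any intake of 8 weeks or less gives 0%, for example start 28 and delivery 36.
- **The loss of contrast is conditional.** A reader might infer that the effect is halved and the sample must be four times larger (1/0.5² = 4). That needs s = 50%, a constant effect from the first sachet, a pure change score and an unchanged SD. With an ANCOVA slope of 0.5 the multiple is 1/0.75² = 1.8, and a delayed effect shrinks the contrast less. No sample size rests on cortisol: the full trial is sized on depressive symptoms.
- **Piece 1 is unharmed.** Comparing it directly between arms does not use the baseline. This stands.
- **The outcome is exploratory.** No success criteria are set for secondary outcomes, their analyses are to be read as preliminary, and the hair criterion in Table 1 concerns only consent to sampling. This stands and limits the severity.

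**Conclusion.** The label on the second segment is wrong as written for any woman whose intake exceeds about 8 weeks, given adjacent pieces. Over the stated 8–14 weeks, 0–75% of that segment grew during the intervention. The mean is about 37.5–50% at the article's 4 weeks per cm, or about 24–34% with calendar months, under the two spreads assumed above.

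The cortisol baseline is therefore partly measured after randomisation. If any effect keeps the same direction throughout intake, a change score or baseline-adjusted contrast is biased toward zero. The size of that bias differs between women and depends on when the effect begins and which analysis is used, so no single figure for lost power is justified. Table 2's t1 metric also does not describe piece 1, which is tied to delivery and not to t1.

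Severity is moderate. The pilot's feasibility and acceptability conclusions and its progression criteria are unaffected.

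**What to change.** - **Cutting instruction.** Position the second segment from each woman's own first-intake and delivery dates: begin at about 1 cm + (weeks of intake)/4 cm from the scalp, take the next 2 cm, and discard the hair between the two segments. For 8 weeks this is 3–5 cm; for 14 weeks it is 4.5–6.5 cm.
- **Short hair.** Treat the baseline as missing where the strand does not reach.
- **Analysis.** Report the unadjusted between-arm comparison of piece 1 alongside the baseline-based one, so that women with short hair are not lost.
- **Table 2.** Relabel the metric as the last 8 weeks of intake versus the 8 weeks before first intake.

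The change costs a laboratory instruction and a line in Table 2. Gestational age at delivery is already a Table 2 item; the first-intake date should be confirmed as recorded. Data management keeps samples until the study is complete, so strands not yet divided can still be cut this way.

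There are two drawbacks. Baselines will be missing for hair shorter than about 5–6.5 cm, and the required length rises with intake duration, so missingness will depend on it. The cut points also remain approximate because the growth rate is approximate.
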